## Abstract

**Background:**

The considerable rise of mental health challenges during the COVID-19 pandemic has had detrimental effects on the public health sector and economy. To meet the overwhelming and growing demand for mental health care, innovative approaches must be employed to significantly expand mental health care delivery capacity. Although it is not feasible to increase the number of mental health care providers or hours they work in the short term, improving their time efficiency may be a viable solution. Virtually and digitally delivering psychotherapy, which has been shown to be efficient and clinically effective, might be a good method for addressing this growing demand.

**Objective:**

This research protocol aims to evaluate the feasibility and efficacy of using an online, digital, asynchronous care model to treat mental health issues that are started or aggravated by stressors associated with the COVID-19 pandemic.

**Methods:**

This nonrandomized controlled trial intervention will be delivered through the Online Psychotherapy Tool, a secure, cloud-based, digital mental health platform. Participants will be offered a 9-week electronically delivered cognitive behavioral therapy program that is tailored to address mental health problems in the context of the COVID-19 pandemic. This program will involve weekly self-guided educational material that provides an overview of behavioral skills and weekly homework. Participants (N=80) will receive personalized feedback from and weekly interaction with a therapist throughout the course of the program. The efficacy of the program will be evaluated using clinically validated symptomology questionnaires, which are to be completed by participants at baseline, week 5, and posttreatment. Inclusion criteria includes the capacity to consent; a primary diagnosis of generalized anxiety disorder or major depressive disorder, with symptoms that started or worsened during the COVID-19 pandemic; the ability to speak and read English; and consistent and reliable access to the internet. Exclusion criteria includes active psychosis, acute mania, severe alcohol or substance use disorder, and active suicidal or homicidal ideation.

**Results:**

This study received funding in May 2020. Ethics approval was received in June 2020. The recruitment of participants began in June 2020. Participant recruitment is being conducted via social media, web-based communities, and physician referrals. To date, 58 participants have been recruited (intervention group: n=35; control group: n=23). Data collection is expected to conclude by the end of 2020. Analyses (ie, linear regression analysis for continuous outcomes and binomial regression analysis for categorical outcomes) are expected to be completed by February 2021.

**Conclusions:**

If proven feasible, this care delivery method could increase care capacity by up to fourfold. The findings from this study can potentially influence clinical practices and policies and increase accessibility to care during the COVID-19 pandemic, without sacrificing the quality of care.

**Trial Registration:**

ClinicalTrials.gov NCT04476667; https://clinicaltrials.gov/ct2/show/NCT04476667

**International Registered Report Identifier (IRRID):**

DERR1-10.2196/24913

## Introduction

### Background and Rationale

The COVID-19 pandemic is a source of high-degree uncertainty, anxiety, and stress, and it is ultimately affecting mental health on a global scale. According to a recent survey, 75% of Canadians have reported feeling anxious, 37% have reported feeling lonely, and 32% have said that they are having a hard time falling asleep because of stressors associated with the COVID-19 pandemic [1]. Previous experience has shown that the psychological scars resulting from public disasters go far beyond the official end of the disaster. For instance, the mental health effects that were observed following Hurricane Katrina lasted for over 4 years after the disaster, with a 35% increase in substance abuse hospitalization in New Orleans [2]. This shows that addressing the mental health aspect of the COVID-19 pandemic is as important as addressing the immediate medical emergency. The increase in demand for mental health care services resulting from the COVID-19 pandemic has come in the backdrop of a system that is already in crisis, which necessitates devising innovative approaches for increasing the current care capacity to cover more patients.

Cognitive behavioral therapy (CBT) could be a promising solution for treating depression and anxiety disorders related to the COVID-19 pandemic. CBT is widely regarded as a first-line treatment for major depressive disorder (MDD) and generalized anxiety disorder (GAD), as supported by randomized controlled trials, meta-analyses, and the recommendations of most clinical guidelines [3-7]. CBT has proven to be effective in relieving depressive and anxiety-related symptoms, improving the overall functioning of patients with such symptoms, and preventing relapses of these conditions [3-5], with long-term effects [6,7]. However, effectively administering CBT through face-to-face or virtual/live (ie, synchronous) methods is very time consuming and costly, and in most cases, such methods are not accessible to many patients. Electronically delivered CBT (ie, nonlive, asynchronous care; e-CBT) could be a viable alternative method for mental health care delivery. E-CBT has proven to be efficacious in treating both anxiety and depressive disorders, with comparable results to in-person therapy [8-11]. E-CBT content can be conveniently accessed anytime and anywhere, thereby providing flexible access to care, even for people who live in remote areas. A major benefit of e-CBT is that by delivering predesigned therapy content, clinicians can skip repeating similar general concepts to multiple patients and reduce their time commitment to a fraction of that in in-person therapy [12,13]. This not only reduces the cost of care delivery, but also allows more people to receive care from existing clinical resources and shortens waiting times. The main disadvantage to using e-CBT as a treatment delivery modality is that some individuals might not have access to the necessary technology (eg, phones, tablets, or laptops) or proper internet connectivity. Furthermore, there are different methods of delivering e-CBT, which range from unguided self-help [14,15] to guided programs that consist of a standardized content delivery modality with support from a mental health professional [12,13,16]. Although these different methods have been shown to be effective to some extent, their efficacy varies depending on the level of care provider engagement during the therapy process [17]. Naturally, as the level of clinical engagement goes higher, so does the cost of therapy, thereby making the therapy less accessible to patients in need. We believe a hybrid solution that combines predesigned content with limited and personalized guidance from a clinician could lower the costs of therapy, increase care capacity, and improve patient outcomes through increased patient engagement. Given the structured nature of CBT, even clinician feedback could follow a predesigned structure to make the process more streamlined.

In this protocol, we aim to develop a scalable online psychotherapy clinic centered around e-CBT to assist patients with stress resulting from the COVID-19 pandemic. The e-CBT program consists of 9 weekly modules that focus on coping skills and building resilience, which are effective in the treatment of mood and anxiety disorders. We will use the Online Psychotherapy Tool (OPTT; OPTT Inc) [18], a secure, cloud-based platform, to interact with patients and deliver therapy. By using the OPTT, all patient information can be kept secure and confidential, while allowing all clinicians on the treatment team to access their patients’ information and communicate with one another through the platform to discuss their patients. We hypothesize that using these psychotherapeutic interventions during the COVID-19 pandemic will improve the quality of life and decrease symptoms of depression and anxiety in the intervention group compared to the control group.

### Objectives

The first objective of this study is to design and implement a scalable online psychotherapy clinic and care plan (ie, content, design, and feedback structure plans) to address mental health problems that started or worsened during the COVID-19 pandemic. The second objective is to evaluate the feasibility and efficacy of treating COVID-19–related mental health problems by offering specific e-CBT modules through an online clinic. The third and final objective is to rapidly disseminate the knowledge gained from this study to other practices, thereby facilitating the effective and reliable scaling of this solution across the community.

## Methods

### Study Design

This clinical trial has a nonrandomized controlled trial design. Participants in the intervention group will be offered a 9-week e-CBT program that is tailored to address mental health problems in the context of the COVID-19 pandemic. Qualitative focus groups will be conducted to gather personal demographic information, as well as information about the feasibility of implementing an online psychotherapy clinic. Additionally, quantitative analyses of online psychotherapy treatment efficacy will be conducted using standardized symptomology questionnaires. All procedures have been approved by the Queen’s University Health Sciences and Affiliated Teaching Hospitals Research Ethics Board.

### Participants

Participants (N=80) aged 18-65 years will be enrolled in the study based on referrals from the Hotel Dieu Hospital and Providence Care Hospital outpatient clinics located in Kingston, Ontario, Canada, and self-referrals from social media and web-based communities. Those referred and interested in participating will provide informed consent before being evaluated by one of the psychiatrists on the research team through a secure video appointment. During this appointment, MDD/GAD diagnoses will be made or confirmed using the Diagnostic and Statistical Manual of Mental Disorders, 5th Edition (DSM-5). Mini-International Neuropsychiatric Interview, Version 7.0.2 DSM-5 will also be administered by a trained research assistant on the team to confirm the diagnosis. Inclusion criteria includes the capacity to consent; a primary diagnosis of GAD or MDD, with symptoms that started or worsened during the COVID-19 pandemic; the ability to speak and read English; and consistent and reliable access to the internet. Exclusion criteria includes active psychosis, acute mania, severe alcohol or substance use disorder, and active suicidal or homicidal ideation. Additionally, to keep the scope of this study focused on the more common challenges that people face during the pandemic, participants will be excluded if mental health problems are secondary to a medical condition. Moreover, if a participant is currently receiving or has received CBT in any format during the past year, they will be excluded to prevent a possible confounding effect between previous CBT treatment and the e-CBT program.

Participants who are eligible for this study will be offered to join the electronic psychotherapy (e-psychotherapy) group. If individuals in this treatment group have been on pharmacotherapy treatment, their medication from 6 weeks prior to the trial and during the 9 weeks of treatment will not get changed. Individuals diagnosed with MDD or GAD who do not wish to participate in the e-psychotherapy group will continue to receive treatment as usual (TAU) and will be part of the control group. TAU is defined as any lifestyle activities and interventions (ie, medication, psychiatric consultation and referrals, exercise, diet, etc) that participants in either group were receiving prior to joining the trial. These activities and interventions will not be changed throughout the course of participants’ participation. Both groups will be stratified by sex, gender, and age.

### Procedures

Participants enrolled in the e-psychotherapy group will participate in a 9-week program that will include a combination of CBT, mindfulness therapy, and problem-based therapy. The content of the e-psychotherapy program will be customized to reflect the challenges that individuals may face during the COVID-19 pandemic and developed into interactive and engaging therapy modules. A sample session has been provided by OPTT Inc [19]. All online sessions and interactions will occur through a secure, online platform called the OPTT.

Each participant will be assigned to a therapist on the research team. During each week, the therapist will assign a predesigned therapy module to their patient through the OPTT on a specific day of the week. Participants will have access to the therapy content at any time throughout the week. Each weekly module will focus on a new topic by covering general information on the topic, providing an overview of the skills associated with the topic, and providing homework, which will be due on a specific day of the week. All content and topics that will be covered are designed to mirror in-person CBT programs. Completing each weekly module will require an average time commitment of 40 minutes, which can be completed all at once or in several blocks of time. The homework will be directly submitted through the OPTT to the clinician, who will then provide personalized feedback to the patient.

In order to maintain care and outcome consistency and streamline the process, therapists will use predesigned session-specific feedback templates to respond to each homework submission. This will also help to save time and costs and make the program more scalable. Therapist feedback will generally follow a certain structure. First, the therapist will start off feedback by valuing the participant’s time and effort. This will help to establish a rapport between the therapist and the participant. Second, the therapist will summarize the previous sessions’ material and remind the participant of what they have learned so far. The information in this section will differ between sessions, but it will remain constant across participants. Third, the therapist will discuss the participant’s homework and provide an evaluation. The therapist will always review the event that the participant used in their homework, so that the participant will know that their therapist has read and paid attention to their unique situation. Fourth, the therapist will discuss what the participant did right and what the participant could have done differently in their homework. Last, the therapist will emphasize their appreciation for the participant’s hard work and sign their name. This will ensure that the connection between the therapist and the participant remains personal. Writing feedback using this structure usually does not take longer than 15-20 minutes for an experienced therapist. A more detailed explanation on this structure can be found in Online Cognitive Behavioral Therapy: An e-Mental Health Approach to Depression and Anxiety, a book by [name] and [name] [20].

Although the homework and clinician feedback are considered the main means of communication between therapists and participants, participants can also communicate with their therapist through a secure chat function that is found directly within the OPTT. This is mainly used to let participants ask further questions about their care, if anything is not clear. Any technical issues will be handled through the OPTT technical support team, which participants will have access to at all times during the program. The patient care team (eg, the therapist and the psychiatrist) will also be able to securely communicate through the OPTT to make decisions regarding each patient’s care path.

The control group will continue receiving TAU for the first 9 weeks of their participation. If control group participants continue to present significant symptoms (ie, <50% reduction in symptoms compared to those in baseline), they will again be offered the option to undergo the e-psychotherapy program or other forms of treatments as deemed necessary.

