### Training

All the therapists are research assistants hired by the research team. These therapists have previous training in psychotherapy, and they will receive further training from one of the psychiatrists involved in the study before they interact with participants. Therapists will learn the standard care pathway, aim, and content of each therapeutic session. Moreover, they will be provided with sample homework from patients and asked to provide feedback as practice for each session. As explained earlier, the feedback templates will vary from session to session, and therapists will personalize each template for each patient’s homework. Training will be provided through webinars and exercises with feedback. Therapists will also be supervised by the lead psychiatrist on the team, who has more than 10 years of experience in in-person and online psychotherapy. After the feedback is prepared by the therapist, the feedback will be read, edited, and approved by the supervisor before it is submitted to the participant.

During the consent process, participants are informed that this program is not to be used as a crisis resource, as therapists cannot be reached at all times through the OPTT platform. In the case of an emergency (eg, suicidal ideation), therapists will be instructed to direct patients to the proper resources (eg, emergency department, crisis lines, etc) and inform their supervisor about such incidents.

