### Data Analysis

Initially, all data will be examined for missing, nonsensical, and outlying variables. Missing data will be treated as missing and not imputed. This will be analyzed on a per-protocol basis. Given the likelihood of participant drop out or withdrawal, we have purposely oversampled our study and control groups to obtain meaningful and statistically significant results at the end of the study. Based on our previous experience with CBT and e-CBT in similar patient populations, we anticipate that up to 30% of participants will drop out by the end of the treatment or TAU phases. Using GAD-7 questionnaire scores as the primary outcome means that a 30% change is considered clinically significant. Therefore, a sample size of 40 participants in each arm of the study will be sufficient for detecting significant results (ie, *P*=.05 and a power of 0.95). In addition, an intention-to-treat analysis will be performed to evaluate completion rates and the clinical effects of participants leaving the trial before completion.

Data collection will occur at 3 separate time points, as follows: at baseline (ie, preintervention), in the middle of the study (ie, week 5), and immediately at postintervention (ie, week 9). Mann-Whitney U tests will be used to compare baseline demographic data between individuals who drop out and those who finish the e-CBT program, and any fundamental differences between completers and noncompleters will be identified. A linear regression analysis for continuous outcomes and binomial regression analysis for categorical outcomes will be performed to identify variables associated with the 2 outcome measures over the 3 measurement time points and to compare the differences between study arms. These analyses will be controlled for demographic variables, such as age and gender.

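### Only the e-CBT arm is nested within therapists, and the stated arm comparison names no therapist effect; its standard error is understated if outcomes correlate within therapist.

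*Protocol article*

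**What the plan says.** - **Therapist assignment.** In the description of the e-psychotherapy group, Procedures states: "Each participant will be assigned to a therapist on the research team". That therapist assigns the weekly modules and responds to the homework over the 9 weeks. Training adds: "All the therapists are research assistants hired by the research team". Neither section gives the number of therapists or a caseload.
- **Control arm.** Procedures: "The control group will continue receiving TAU for the first 9 weeks of their participation". No trial therapist is described for this arm.
- **Analysis.** Data Analysis: "A linear regression analysis for continuous outcomes and binomial regression analysis for categorical outcomes will be performed", partly "to compare the differences between study arms". On adjustment: "These analyses will be controlled for demographic variables, such as age and gender". No therapist term, random effect or cluster-robust standard error is named, and no design effect is mentioned with the 40 per arm.
- **Limits on therapist variation.** Procedures: "therapists will use predesigned session-specific feedback templates to respond to each homework submission". Training adds that a supervisor edits and approves the feedback before participants receive it.
- **Room for therapist variation.** Therapists tailor the templates to each participant's homework (Training) and can be reached by chat (Procedures). No supervisor review of chat is described.

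**The concern.** Patients who share a therapist can share part of their outcome. In the e-CBT arm this adds a between-therapist component to the variance of the arm mean; the control arm has no counterpart. Ordinary regression with demographic covariates takes residuals as independent between patients and leaves that component out. This is distinct from the correlation among one person's three assessments.

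At stake are the width of the confidence interval for the e-CBT versus TAU difference and the true type I error. The scope of the claim is also affected. The Objectives section aims to scale the program to other practices, so the intended inference reaches beyond the therapists who took part, and variation between therapists belongs in the uncertainty.

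**Working it through.** **Inputs from the protocol article (Data Analysis):** 40 per arm; significance level .05 (sidedness not stated, two-sided assumed); power 0.95; dropout up to 30%, which leaves 40 × 0.70 = 28 completers per arm.

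**Assumptions, because the article gives no figure:** number of therapists k from 2 to 10; ICC from 0 to 0.10; equal caloads within the e-CBT arm; equal total variance in the two arms; normal approximation.

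**The plan's own figure.** The 40 per arm can be neither reproduced nor refuted, because no GAD-7 mean or standard deviation is given. Solving backwards, the implied standardized difference is d = (1.960 + 1.645) × √(2/n). This is 0.81 at n = 40 and 0.96 at n = 28.

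**Formulas**, with m = n/k patients per therapist:
- Design effect in the e-CBT arm: DE = 1 + (m − 1) × ICC.
- True SE / model SE: r = √((DE + 1)/2), since only one of two equal arms is inflated.
- Understatement of the SE: 1 − 1/r.
- Actual two-sided alpha: 2 × (1 − Φ(1.96/r)).
- Power of a test held at a true 5% level, where the plan intends 0.95: Φ(3.605/r − 1.96), with 3.605 = 1.960 + 1.645.

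**Worked case:** n = 40, k = 4, ICC 0.05. Then m = 10, DE = 1 + 9 × 0.05 = 1.45 and r = √(2.45/2) = 1.107. The model SE is 1 − 1/1.107 = 9.6% too small, alpha is 0.0766 and power is 0.90.

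| n per arm | k | ICC | DE | r | SE too small by | Actual alpha | Power |
|---|---|---|---|---|---|---|---|
| 40 | 4 | 0 | 1.00 | 1.000 | 0% | 0.0500 | 0.95 |
| 40 | 4 | 0.01 | 1.09 | 1.022 | 2.2% | 0.0552 | 0.94 |
| 40 | 4 | 0.02 | 1.18 | 1.044 | 4.2% | 0.0605 | 0.93 |
| 40 | 4 | 0.05 | 1.45 | 1.107 | 9.6% | 0.0766 | 0.90 |
| 40 | 4 | 0.10 | 1.90 | 1.204 | 17.0% | 0.1036 | 0.85 |
| 40 | 10 | 0.01 | 1.03 | 1.007 | 0.7% | 0.0517 | 0.95 |
| 40 | 10 | 0.05 | 1.15 | 1.037 | 3.6% | 0.0587 | 0.94 |
| 40 | 2 | 0.05 | 1.95 | 1.214 | 17.7% | 0.107 | 0.84 |
| 28 | 4 | 0.05 | 1.30 | 1.072 | 6.7% | 0.0676 | 0.92 |

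**Cross-check by simulation.** This used 40,000 null trials per scenario and a two-sample t-test. With 40 per arm and 4 therapists, the rejection rates were 6.1%, 7.5% and 10.0% at ICC 0.02, 0.05 and 0.10. With 2 therapists and ICC 0.05 the rate was 10.5%. With 28 per arm, 4 therapists and ICC 0.05 it was 6.9%. These agree with the formulas.

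**The case against.** The strongest objection is that this argues from silence. The source is a condensed article, and an analysis plan not shown here could contain a therapist term or robust standard errors. The article nowhere says that patients are treated as independent, and its covariate list is open-ended. This stands as a limit on what can be asserted. It does not remove the point, because the article does fix the model family and the kind of covariate, and that model as stated does not match the one-sided nesting the article describes.

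A reader might infer three stronger things that the text does not support:
- **That there are only a few therapists.** No number or caseload is given. One team of research assistants under close supervision is consistent with a small number but does not establish it.
- **That the standard error is certainly too small.** This needs an ICC above zero; at zero there is no error.
- **That personalized feedback proves an ICC above zero.** Tailoring to each homework is variation between patients. It leaves room for differences between therapists without showing them.

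Common modules, templates, training and supervisor editing all point to a small ICC, where the effect is slight. This also stands. So does the objection to the remedy: with very few therapists the variance component is poorly estimated and a random-intercept model is unreliable.

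Finally, controls are people who did not wish to join e-CBT (Participants), and the Discussion concedes the nonrandomized design. That selection bias is the larger threat and no standard-error correction repairs it. The two problems are separate, however, and the larger does not excuse the smaller.

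**Conclusion.** The point holds conditionally. The partial nesting is in the text, and the stated arm comparison makes no provision for it. For any ICC above zero with shared therapists, the error is anti-conservative.

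Its size rests on two quantities that the article does not give. At 40 per arm, as k falls from 10 to 2, the model SE is 0.7% to 4.4% too small at ICC 0.01 and 3.6% to 17.7% too small at ICC 0.05. The templated, supervised feedback makes the low end more plausible; with 4 therapists and ICC 0.01, alpha is about 0.055 instead of 0.05. An alpha near 0.10 needs an ICC near 0.10 with 4 therapists, or about 2 therapists at ICC 0.05, and nothing in the article supports either combination. The plan's sample size is neither confirmed nor contradicted by this check.

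**What to change.** - Keep the therapist identifier in the analysis file, and report the number of therapists and each caseload.
- If there are enough therapists to estimate the variance, compare the arms with a therapist random intercept in the e-CBT arm only, with small-sample degrees of freedom.
- If there are too few, keep the stated regression as the main analysis. Add a sensitivity analysis with the SE of the arm difference inflated over ICC 0.01 to 0.10, and a leave-one-therapist-out check. For unequal arms n₁ (e-CBT) and n₀ (control), the multiplier is √[(DE/n₁ + 1/n₀)/(1/n₁ + 1/n₀)], which reduces to r above when the arms are equal.
- State in advance which of the two routes applies, once the number of therapists is known and before outcomes are examined.

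The cost is a few sentences of analysis wording and a few lines of code, with no change to design or recruitment. The downside is a somewhat wider confidence interval and, with few therapists, fewer degrees of freedom. The change does nothing for the selection bias in the control group, which needs separate treatment.
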